## Abstract

**Background:**

Translation of knowledge and skills from classroom settings to clinical practice is a major challenge in healthcare training, especially for behavioral interventions. For example, screening, brief intervention, and referral to treatment (SBIRT) is a highly-promoted approach to identifying and treating individuals at risk for alcohol or drug problems, yet effective, routine use of SBIRT has lagged.

**Objective:**

The objective of this paper is to describe the development, pilot testing, and trial protocol of a mobile app based on the theory of planned behavior (TPB) to promote SBIRT skill translation and application.

**Methods:**

Intended for use after classroom training occurs, the mobile app has three primary functions designed to increase behavioral intent to deliver SBIRT: (1) review skills (ie, address knowledge and beliefs about SBIRT), (2) apply skills with patients (ie, build confidence and perceived behavioral control), and (3) report performance data (ie, increase accountability and social norms and/or influence). The app includes depression and anxiety screening tools due to high comorbidity with substance use. A randomized controlled trial (RCT) is in progress among health and social service learners (N=200) recruited from 3 universities and 6 different training programs in nursing, social work, internal medicine, psychiatry, and psychology. Participants are randomized to SBIRT classroom instruction alone or classroom instruction plus app access prior to beginning their field placement rotations. TPB-based data are collected via Qualtrics or via the mobile app pre-post and SBIRT utilization, weekly for 10 weeks. Key outcomes include the frequency of and self-reported confidence in delivery of SBIRT.

**Results:**

Beta testing with advanced practice nursing students (N=22) indicated that the app and its associated assessment tools were acceptable and useful. The system usability scale (SUS) mean was 65.8 (n=19), which indicated that the SBIRT app was acceptable but could benefit from improvement. Indeed, modifications were implemented prior to starting the trial. Enrollment of trial participants began in September 2016. Results are expected by December 2017.

**Conclusions:**

This report describes the process of TPB-based app development and testing, and the protocol for a RCT to determine the effectiveness of the app in enhancing skill translation. If effective, this approach could improve SBIRT implementation, fidelity, and clinical outcomes.

## Introduction

The transition from learning clinical skills to sustained changes in health provider behavior is a known problem. Even when evidence-based treatments are available and implementation decisions have been made, workforce development and sustained intervention delivery present formidable challenges [1]. For example, maintaining fidelity to evidence-based treatments (eg, cognitive behavioral therapy [2]), often requires strategies to support ongoing learning such as supervision and coaching [3]. Providers must learn the new skills, practice the skills, build confidence (in themselves and the intervention), and be able to change past practice norms all within an environment that supports such changes. However, these personnel-intensive strategies can be costly and time-consuming, and have limited reach due to resource constraints. Yet with effective strategies to support skill translation [4,5], behavioral healthcare providers can effectively deliver the interventions they are trained to use. Thus, a major challenge for the implementation of evidence-based behavioral practices concerns how to deliver cost-effective support for skill translation in healthcare.

Screening, brief intervention, and referral to treatment (SBIRT) for unhealthy alcohol and drug use is an important example of a widely-trained skill that has fallen short in translation [6]. SBIRT is designed to reach individuals in health or social service settings who use substances at a range of levels, including those who may not yet meet criteria for alcohol or drug use disorders. Components include screening for hazardous drinking and drug use and related problems, delivering brief motivational interviewing-based interventions for patients at low to moderate risk, and providing referrals to addiction specialty care for those with significant problems [7]. Available evidence supports the effectiveness of screening and brief intervention in addressing hazardous drinking within primary care [8-10], although evidence for effectiveness in reducing drug use is weak and trials have been mixed [11-14]. Based on the strength of this literature, national practice guidelines for SBIRT integration into primary care and other health and social service settings have been developed [15,16].

In spite of these practice recommendations and a proliferation of SBIRT training programs, optimal skill translation to direct clinical care remains unrealized. Trainees often demonstrate classroom skill proficiency yet fail to use SBIRT in subsequent clinical placements. Commonly cited barriers to translation include provider attitudes about substance use interventions, problems with knowledge recall at the point-of-care, lack of confidence, inadequate knowledge of referral resources, as well as structural barriers in clinical settings such as limited time and competing medical demands, especially in primary care [17-19]. Studies of SBIRT skill translation and implementation have found a decrease in post-training SBIRT delivery rates over time [20,21], variability in delivery rates across health disciplines [22,23], and low fidelity to screening questions [24]. Fewer than one in six Americans report being asked about or discussing their drinking with a health professional [25], and screening is rarely conducted in US primary care settings [26] outside the Veteran’s Affairs Health System [27]. Similarly, a minority of patients in mental health settings report that providers advise them to reduce hazardous drinking or drug use [28], and a recent meta-analysis demonstrated that fidelity to motivational interviewing by clinicians is often poor [29]. These findings highlight the importance of improving skill translation in real-world health and social service settings.

Digital learning tools have been incorporated into some SBIRT training programs but have not been effectively integrated with clinical care. For example, online training modules sometimes supplement didactic presentations and demonstrations, role play with feedback, and patient encounters [30-32]. With some variability, these digital health training components have been rated as relevant and useful by trainees. Outcome studies have found that such training resulted in increased confidence in SBIRT delivery and more positive attitudes towards patients who use alcohol [33]. Yet digital tools such as online learning models have not supported skill translation over time. To our knowledge, the one SBIRT mobile app that is currently available does not incorporate background materials targeted towards trainees (eg, review of prevalence of substance use and evidence for SBIRT efficacy), nor does it include detailed support in conducting screening, delivering interventions, and treatment referral resources [34]. If designed with skill translation in mind, a point-of-care mobile app with this additional content could help providers apply newly learned SBIRT skills [1].

In other health delivery contexts, mobile apps are gaining acceptance and appear to enhance training. Bullock et al (2015) found that providing a mobile app containing the [name] software with 5 key medical textbooks (the iDoc app) to newly qualified doctors increased access to reference materials and was effective in supporting learning and practice [35]. The use of mobile technology, including medical apps in nursing education, has demonstrated success in improving learning outcomes and learner confidence [36]. Tablet-based patient self-administered alcohol and drug screening [37,38] and intervention [39] can increase efficiency in healthcare settings. Yet prior studies have not examined how mobile apps may enhance SBIRT training and skill translation.

Theoretical models identifying barriers and facilitators regarding learning and skill translation may help guide the development of intervention strategies to enhance skill transfer and implementation. On the level of individual provider (or learner) behavior, the theory of planned behavior (TPB) provides a well-validated, conceptual model that identifies both internal and external key factors that could influence SBIRT skill translation [40]. In the TPB model, behavioral intent (to perform the behavior of interest) is determined by attitudes and/or beliefs about the behavior, perceived social norms, and perceived behavioral control. The TPB is contextualized for SBIRT skill translation in Figure 1, allowing us to assess learners on each of these variables and to provide matched interventions as needed to promote SBIRT usage. For example, we provide information on the extent of substance use and related problems, and SBIRT efficacy to shape attitudes regarding the value of screening and treatment. We provide information on standards of care (eg, that SBIRT has been recommended by the US Preventive Task Force and many health professional bodies) to influence perceived social norms. Moreover, we provide tools to support practicing SBIRT to positively impact both attitudes and perceived behavioral control such as trainees’ confidence in successfully performing SBIRT and integrating it into clinical care.

The aim of this paper is to describe the process of TPB-based mobile alcohol and drug SBIRT app development, beta testing, and protocol for a randomized controlled trial (RCT) comparing health professional learners with access to the app (intervention arm) to learners without access to the app (control arm). We hypothesize that participants in the intervention arm will be more likely to deliver SBIRT in clinical placements than those in the control arm and will be more likely to report intention to deliver SBIRT in the future. We also hypothesize that intervention participants will report more positive beliefs about SBIRT, greater knowledge, and greater perceived control over SBIRT delivery in clinic.

**Figure 1 figure1:**
[figure not shown]
Theory of planned behavior as applied to screening, brief intervention, and referral to treatment (SBIRT) skill translation. Model adapted from Ajzen (1991). SUD: substance use disorder; SUS: system usability scale.

## Methods

### App Development

An interprofessional team worked to develop the TPB-based app. The team was comprised of faculty members with prior research expertise in SBIRT training and implementation and included two clinical psychologists with doctorate degrees, an internal medicine physician, an advanced practice nurse with a doctorate degree, and an experienced project manager. Existing mobile apps were identified to determine needs in the field and to learn about components often emphasized in enhancing behavior change, for example, mobile apps for SBIRT [34], Change Talk for Childhood Obesity [41], and Epocrates [42]. Digital product design principles were reviewed including the creation of a product vision and end goal, character sketches of potential users (“personas”), features of currently available products, and emerging mobile app tools that simplify the user interface and promote app usage [43]. The app’s purpose and vision evolved based on faculty and learner responses to initial designs. As follow-up to a needs assessment questionnaire, faculty members from different training programs were asked about the potential utility of a mobile app to increase learners’ use of SBIRT. Learners identified specific features and content they wanted while using the app during clinic placements. For example, learners wanted point-of-care screening tools and SBIRT frequency of use measures integrated directly into the app.

Based on this initial feedback, the app was designed as a tool for learners to use at their clinic sites that could function as both an SBIRT information resource and as a tool to assist in skills practice and implementation. Content was designed to primarily address alcohol and drug use, but screeners for depression and anxiety, which commonly co-occur with problematic substance use, were added to broaden the scope of the app and to increase its perceived value to both learners and preceptors. A key design principle was to ensure the app fit within the clinical environment and did not disrupt other training or patient care activities. Because of data security concerns and the range of service settings and medical record systems in which trainees could use SBIRT, the app was not designed to connect with local electronic health records and does not record any protected health information. Given the expense and complexity of integrating screening into healthcare records, with which the faculty had prior experience (eg, integration of alcohol screening into electronic health records in Kaiser Permanente Northern California [22]), and the fact that not all learners are placed in settings that have electronic records, we anticipated that keeping the app separate from patient record systems would maximize learner flexibility across various clinical placements and assuage concerns about loss of patient privacy.

Flow diagrams and wireframes (page schematics and screenshots) were drafted to correspond to the key components of the app. Open Health Network app developers [44] were selected as a development partner based on their prior experience in developing mobile apps for healthcare. The wireframes were given to the developers, who provided an initial alpha version. Team members tested the alpha version individually and worked with the developers to continue refining the flow and content for subsequent beta testing.

### Beta Testing

Once the final beta version of the app was developed, our team chose a small cohort of nurse practitioner learners (N=22) at the University of San Francisco to beta test the app for 3 months. Our testers included learners in an advanced practice nursing training program who were enrolled in a clinic placement. Learners completed the questionnaires and processes to be used in the larger RCT. Full TPB-based surveys (see “Pre/Post Assessment Questions”) were repeated at the end of the beta-testing period, followed by a debrief focus group. The team tested and refined the app prior to starting the controlled trial. Beta testing results are described below.

### Randomized Controlled Trial

#### Study Design

The study is a RCT of an SBIRT mobile app to facilitate skill translation from classroom to clinical placements among 200 graduate and post-graduate learners (Figure 2). Following SBIRT instruction, participants are enrolled and randomized to the experimental (use of the app) or control (no access to the app) condition. All participants complete self-report measures over the study duration (10 weeks). The trial runs from fall 2016 through spring 2017.

**Figure 2 figure2:**
[figure not shown]
Overall study design for the development and testing of an alcohol and drug screening, brief intervention, and referral to treatment (SBIRT) mobile app to enhance skill translation. Figure adapted from the CONSORT Group.

#### Setting

The trial is being carried out at 3 sites, among 6 training programs: San Francisco State University (Social Work and Nursing), University of California, San Francisco (Internal Medicine and Psychiatry), and University of San Francisco (Nursing and Psychology). Institutional review boards at the 3 sites approved all study procedures. The study is not registered with ClinicalTrials.gov because the design does not include a collection of clinical data or patient-level outcomes.

#### Participants

Study participants (trainees, N=200) are adult health professional learners in one of the designated training programs. Participants must have had prior classroom or online training in SBIRT within the past year and may not have previously used an SBIRT app. For learners who have not yet completed classroom-based SBIRT instruction, they are required to complete the following 3 online training modules developed by the research team: (1) Introduction to SBIRT, (2) Screening, and (3) Brief Intervention. The learner must be enrolled in a field placement and is required to have a mobile device to be in the study (Android or iOS). Field placements include a range of private and public healthcare and social service agencies in the San Francisco Bay Area.

#### Recruitment and Randomization

Project faculty identified SBIRT educators at the participating training programs and received permission to recruit students. Students are recruited during scheduled classroom time using a detailed information sheet that specifies expectations, timing, and types of data to be collected. Absent learners are invited to participate via email recruitment. Participants provide informed consent to participate either live in classroom settings or via email.

Standard randomization procedures used in behavioral intervention studies are followed [45] using a variable block size with a 1:1 allocation to the intervention or control arm design. These procedures are carried out by the study project manager. Learners are assigned an identification number that is used for the randomization. A Web-based randomization tool is used to generate group assignments. Randomization is stratified by training program in order to have an even distribution of learners in the intervention and control groups from each program.

#### Intervention Arm

Participants in the intervention group are asked to download the app, use it in their clinical rotations (either on their personal mobile phones or tablets), and complete periodic questionnaires via a Qualtrics link. The learners have the opportunity to use the app as much as they need to review SBIRT, receive guidance on structured steps in SBIRT delivery, and receive tailored recommendations on what they can do to improve. We included modest incentives for app use to maximize our ability to measure the potential effects of app use in the trial.

#### Control Arm

Participants in the control group do not download or use the mobile app in their practicum placements but have access to usual teaching materials and supervisors. Control participants complete periodic questionnaires via a Qualtrics link throughout the study period. Upon completion of the study, they are invited to download and use the app at their discretion.

#### Data Collection

At baseline, all participants answer a TPB-based questionnaire via Qualtrics (control) or directly on the app (intervention). At the end of each week, all participants are asked to respond to a brief Qualtrics survey about how often they used SBIRT either by text message (short message service, SMS) or by email. Upon completion of their clinical rotation, all learners are asked to repeat the original TPB-based questionnaire and to provide general feedback about either the app usage (intervention) or their general satisfaction with SBIRT (control).

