### Pre-Post Assessment Questions

The team developed a 22-item questionnaire based on the TPB model. Likert-scaled items assess attitudes and beliefs including importance and efficacy of SBIRT, perceived patient willingness to participate in SBIRT, substance use epidemiology and clinical significance, and subjective norms and perceived behavioral control in the clinic setting. Three items assess confidence in the respondents’ ability to screen for alcohol or drug use problems, deliver a brief intervention, and to make referrals. One item assesses intent to perform SBIRT “whenever possible in my clinical/field placement.” All participants complete this questionnaire at baseline and again at 10 weeks. For intervention participants, baseline TPB responses are used to tailor their app experience by making specific recommendations of what the learner might need to review within the app’s library.

The system usability scale (SUS) [46] is a 10-item Likert scale instrument developed to measure aspects of usability including system complexity and need for support and training. It yields a single score ranging from 0 to 100. Intervention group participants complete this measure at follow-up.

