### Intervention

#### Design and Function

The SBIRT app has the following three primary functions to address TPB concepts: (1) Review SBIRT skills (to help change beliefs and attitudes), (2) Apply SBIRT skills in clinic practice (to help impact attitudes, perceived behavioral control), and (3) Report SBIRT use (to report norms, as well as study outcomes). A fourth component, the Tools section, includes additional reference material and links (Figure 3). After downloading the app, intervention learners create an account and complete the pre-TPB survey. Immediate TPB results are given to the learners along with tailored recommendations on what they should do next. For example, if learners score low on SBIRT knowledge, they are directed to the Review section. A progress checklist in the Tools section reminds them of “homework” they still need to complete. Throughout the study intervention learners are reminded to use the app via the weekly SBIRT usage surveys and periodic text messages promoting app usage.

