#### Report

The Report section was originally conceptualized as a library of tools for instructors and clinical preceptors to track and evaluate their learners. We initially included a collection of pre-post surveys and weekly SBIRT usage items that intervention participants would complete. In order to standardize the data collection procedures across control and intervention participants, all weekly SBIRT usage surveys were completed via Qualtrics. Intervention participants still completed the pre-post TPB surveys and final satisfaction surveys on the app. However, instructors do not receive reports regarding use of the app or SBIRT by learners.

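### The TPB questionnaire is completed in the app by the intervention arm and on Qualtrics by controls, with the intervention baseline taken after allocation, so mode cannot be separated from arm for the TPB outcomes

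*Protocol article*

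**What the plan says.** The protocol article places randomization right after training: "Following SBIRT instruction, participants are enrolled and randomized to the experimental (use of the app) or control (no access to the app) condition" (Study Design). No TPB measurement is placed before that step.

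For the baseline, "all participants answer a TPB-based questionnaire via Qualtrics (control) or directly on the app (intervention" (Data Collection). In the intervention arm the order is explicit: "After downloading the app, intervention learners create an account and complete the pre-TPB survey" (Design and Function). The same section adds that "Immediate TPB results are given to the learners along with tailored recommendations on what they should do next", and Pre-Post Assessment Questions says that "baseline TPB responses are used to tailor their app experience by making specific recommendations".

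For follow-up, the Report section says "Intervention participants still completed the pre-post TPB surveys and final satisfaction surveys on the app". Just before that, it says of the weekly delivery counts: "In order to standardize the data collection procedures across control and intervention participants, all weekly SBIRT usage surveys were completed via Qualtrics".

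The Intervention Arm section also says that these learners "complete periodic questionnaires via a Qualtrics link", without naming which questionnaires. Data Collection gives no mode for the 10-week TPB form.

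**The concern.** The abstract names self-reported confidence in delivery as one of two key outcomes. The weekly survey collects only counts, so confidence comes from three TPB items and intent from one more. The Introduction hypothesizes between-arm differences in intent, beliefs and perceived control, and the Analyses section compares TPB measures.

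These outcomes are measured by a different route in each arm, at both time points. Three consequences follow:

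- A difference in TPB scores may reflect the app, the way the form is presented and answered, or both. No regression model can separate the two, because no learner in either arm is measured in the other mode.
- The intervention arm's baseline is taken once allocation is known and the app is installed. It is not a pre-randomization value and cannot safely be treated as one in adjustment.
- Supplying TPB data requires installing an app in one arm and opening a link in the other. If learners who never install are less engaged, their absence could flatter the app.

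The weekly survey was moved to one platform for exactly this reason, and the TPB form was not. Tailoring needs the baseline answers, but it gives no reason to keep the 10-week form in the app.

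**Working it through.** **Sequence and mode, set side by side**

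| Step | Control | Intervention |
|---|---|---|
| Randomization (Study Design) | after instruction | after instruction |
| Access to app (Control Arm; Design and Function) | none during the study | download, create account |
| Baseline TPB (Data Collection; Design and Function) | Qualtrics | app, after download |
| Weekly delivery counts (Report; Utilization) | Qualtrics | Qualtrics |
| 10-week TPB (Report) | Qualtrics (implied; no app access) | app |

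No single sentence states that the baseline follows randomization. It must do so in the intervention arm, because the mode depends on the assigned arm and the app is reached only after assignment.

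**Size of a mode shift (illustration)**

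The article gives N=200 and 1:1 allocation, hence about 100 per arm. It gives no alpha, SD, effect size or non-response rate, so there is no stated figure to reproduce. Assumptions: two-sided 5% test, SD 1, no true effect, normal approximation, and a mode shift m in the app arm of 0.1, 0.2 or 0.3 SD.

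1. Follow-up-only comparison. SE = √(2/100) = 0.141. Shift/SE = 0.71, 1.41, 2.12. Error = 1 − Φ(1.96 − m/SE) + Φ(−1.96 − m/SE) = 0.109, 0.293, 0.564.
2. Baseline-adjusted comparison, same shift at both times, pre-post correlation ρ. The bias left is m(1 − ρ) and the SE is 0.141 × √(1 − ρ²). With ρ = 0.5 assumed, bias = 0.05, 0.10, 0.15 and SE = 0.122, so error = 0.069, 0.129, 0.232. Over ρ = 0.3 to 0.7, the middle case (m = 0.2) runs from 0.180 to 0.091.
3. Change score, same shift at both times. Bias = m − m = 0, so error stays at 5%.

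For scale, the difference detectable with 80% power is (1.96 + 0.84) × 0.141 = 0.40 SD.

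**Size of a missing-data effect (illustration)**

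Assume a fraction f of the intervention arm gives no TPB data, that these learners would score 0.5 SD below the rest, and that controls are complete. Bias = 0.5f and SE = √(1/(100(1 − f)) + 1/100).

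- f = 10%: bias 0.05 SD, error 0.064
- f = 20%: bias 0.10 SD, error 0.102
- f = 30%: bias 0.15 SD, error 0.161

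Complete controls is a simplification that makes these figures an upper case for the given f. Controls can also fail to answer.

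**The case against.** Both versions are self-completed electronic forms of the same 22 items, so any mode effect may be small. The pre-post structure keeps each arm in one mode throughout, so a constant shift cancels in a change score. This stands, and it is why the 11%, 29% and 56% figures cannot be read as the trial's error rate. The Analyses section does not say whether the TPB comparison is follow-up-only, baseline-adjusted or a change score. The cancellation also requires the shift to be the same at both times, which the design gives no means of checking.

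Four stronger readings are tempting, and the documents do not support them.

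- *Learners who stop using the app have no TPB data by design.* They already have a baseline, taken just after download. They are still asked for the final form and paid US $20 for it. Only those who never install plausibly lack everything, and the article does not rule out a Qualtrics fallback even for them.
- *Missing data do differ by arm, in the app's favour.* No non-response rate is given for either arm, so both the existence and the direction of a difference are untested.
- *Score feedback contaminates the measurement.* Feedback comes after the baseline answers and cannot change them. Tailoring is part of the intervention, so its later influence on TPB scores belongs to the effect under test.
- *The delivery result is compromised.* Weekly counts use one platform in both arms.

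The reference to periodic Qualtrics questionnaires in the Intervention Arm section could suggest that TPB follow-up is also on Qualtrics. It most naturally means the weekly surveys, and the Report section is explicit that the TPB forms were in the app.

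**Conclusion.** The concern holds for the TPB outcomes: confidence, intent, beliefs, norms and perceived control. Mode is fully aliased with arm at baseline and follow-up, and the intervention baseline is a post-allocation measurement. Differential missing data, chiefly from learners who never install, is a structural risk and no more than that.

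The size is unknown. Under assumed shifts of 0.1 to 0.3 SD and 100 per arm, the false-positive rate runs from 5% (change score, constant shift), through about 7% to 23% (baseline adjustment, correlation 0.5), to about 11% to 56% (follow-up only). Every one of these figures rests on assumed inputs. They show how much depends on an analysis choice and on an untestable constancy, not how biased the trial is. The point should be fixed. It does not threaten the randomized comparison of SBIRT delivery.

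**What to change.** **New enrollees.** Give everyone the existing Qualtrics TPB form at consent, before the allocation is generated. Give everyone the same Qualtrics form at 10 weeks, whether or not they installed the app. Run the app's tailoring separately, either by importing the Qualtrics answers or by repeating the items in the app as non-study data.

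**Learners already enrolled with an in-app baseline, or who never installed.** Offer Qualtrics at 10 weeks at least to those who did not install the app. If the follow-up mode is changed for the others, state openly that the intervention arm then changes mode between baseline and follow-up while controls do not, which removes the cancellation in change scores. Flagging baseline mode does not solve this, because the flag coincides with arm among these learners.

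**Reporting.** Present the TPB results with a sensitivity analysis restricted to learners measured in one mode. In practice that means both arms randomized after the change, so that the comparison stays randomized. State that the issue does not extend to weekly delivery.

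**Cost.** Small: an existing form is reused, and consent, baseline and allocation are reordered. Intervention learners may answer 22 items twice if import is not possible. Early enrollees remain non-comparable on baseline mode, and the single-mode analysis will use fewer than 200 learners.

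**What stays open.** Learners know their arm at 10 weeks, so expectation effects on self-report remain whichever platform is used.
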